# Generalization of fear of movement-related pain and avoidance behavior as predictors of work resumption after back surgery: a study protocol for a prospective study (WABS)

**DOI:** 10.1186/s40359-022-00736-5

**Published:** 2022-02-22

**Keywords:** Low back pain, Back surgery, Postoperative pain, Predictors of return to work, Fear of movement-related pain, Avoidance, Fear generalization, Avoidance generalization, Disability, Quality of life

## Abstract

**Background:**

Previous studies indicated that about 20% of the individuals undergoing back surgery are unable to return to work 3 months to 1 year after surgery. The specific factors that predict individual trajectories in postoperative pain, recovery, and work resumption are largely unknown. The aim of this study is to identify modifiable predictors of work resumption after back surgery.

**Methods:**

In this multisite, prospective, longitudinal study, 300 individuals with radicular pain undergoing a lumbar decompression will be followed until 1-year post-surgery. Prior to surgery, participants will perform a computer task to assess fear of movement-related pain, avoidance behavior, and their generalization to novel situations. Before and immediately after surgery, participants will additionally complete questionnaires to assess fear of movement-related pain, avoidance behavior, optimism, expectancies towards recovery and work resumption, and the duration and severity of the pain. Six weeks, 3 months, 6 months, and 12 months after surgery, they will again complete questionnaires to assess sustainable work resumption, pain severity, disability, and quality of life. The primary hypothesis is that (generalization of) fear of movement-related pain and avoidance behavior will negatively affect sustainable work resumption after back surgery. Second, we hypothesize that (generalization of) fear of movement-related pain and avoidance behavior, negative expectancies towards recovery and work resumption, longer pain duration, and more severe pain before the surgery will negatively affect work resumption, pain severity, disability, and quality of life after back surgery. In contrast, optimism and positive expectancies towards recovery and work resumption are expected to predict more favorable work resumption, better quality of life, and lower levels of pain severity and disability after back surgery.

**Discussion:**

With the results of this research, we hope to contribute to the development of strategies for early identification of risk factors and appropriate guidance and interventions before and after back surgery.

*Trial registration* The study was preregistered on ClinicalTrials.gov: NCT04747860 on February 9, 2021.

**Supplementary Information:**

The online version contains supplementary material available at 10.1186/s40359-022-00736-5.

## Background

### Low back pain

Low back pain (LBP) is globally a common health condition and is one of the main reasons people consult a physician [1–4]. It is considered as “*pain, muscle tension or stiffness localized below the costal margin and above the inferior gluteal folds”* [5, p. 1]. Acute LBP is a highly prevalent symptom, affecting 80% of the population at least once in their lifetime [6]. In 10% of the cases, LBP may be caused by a structural pathology such as a fracture, an inflammatory disorder, or a deformity [7]. The most common form of LBP, however, is pain in the lumbar area without a known pathoanatomical problem [8, 9]. For most individuals, the clinical course of LBP is acute and benign [10, 11], with them recovering spontaneously within a few weeks [12]. However, in about one-third of the individuals the pain persists beyond healing time and becomes chronic [11, 13, 14]. Chronic pain is defined as pain that persists or recurs for more than 3–6 months [15, 16]. Due to its persistence, chronic pain can have a detrimental impact on different aspects of life. A subgroup of individuals experiences difficulties in daily life activities and physical impairment [17, 18]. In 2015, the worldwide point prevalence of individuals affected by activity-limiting LBP was estimated at 7.3% [19]. Globally, LBP is also one of the leading causes of years lived with disability [20]. Chronic pain may also affect the psychological wellbeing and mental health of individuals, and often coexists with anxiety and depression [16, 21, 22]. Individuals might, in addition, experience social isolation due to their limitations in maintaining social, family, and sexual relationships [16, 17, 23]. On top of that, chronic pain is a major source of economic burden. Previous studies found that LBP is one of the main reasons for activity limitation, work absence, and even work loss [24–29]. Besides the personal burden, chronic pain entails a huge economic cost for the society due to reduced work efficiency, the use of health care, and sick leave [24, 28, 30–34].

### Back surgery

Over the past decades, the number of back surgeries in Belgium substantially increased. Du Bois et al. [35] reported a rise of 44% from 2001 through 2009 in Belgium. In the past decade, this increase was less pronounced and dropped to 0.44% between 2009 and 2019. From 2017 until 2019, there was even a small decrease of 1.40% [36]. Nevertheless, the number of spine surgeries is still considerable. In 2019, a total of 38,123 spine surgeries were performed. There is however no unequivocal evidence that surgery is the best solution, especially for the treatment of LBP [37]. Studies have found that even after anatomically successful surgery, 10 to 40% of the individuals continue to report pain complaints [38]. A subgroup of individuals undergoing surgery will also be unable to return to work after back surgery. Rates of postoperative return to work differ strongly and vary between 50 to 90% [39]. Recent studies reported that 82% of the individuals were able to return to work 3 months after back surgery [40, 41]. Also in Belgium, Du Bois and Donceel [42] found that 20% of the individuals were unable to resume work 1 year after a lumbar discectomy surgery. Although this considers only a minority of individuals with back pain and radicular pain, they represent a considerable burden to the society [13]. In those individuals, the complaints do not resolve despite anatomical successful surgery. Possible reasons are that psychological and social factors might overrule the effects of surgery, or the specific type of surgery might not have been the right solution for that particular spinal pathology. However, the mechanisms underlying the transition from acute to chronic pain remain poorly understood.

### Mechanisms of chronic pain

The central premise of the current research project is the clinical observation that for some individuals, there seems to be no clear association between recovery of anatomical damage and reduction of pain complaints. The term "Failed Back Surgery Syndrome" (FBSS), for example, refers to persistent axial or peripheral pain following an anatomically successful surgical procedure [43]. In addition, people with chronic back pain often have no identifiable anatomical lesions, or the associated pain severity, affective distress, and disability levels dominate the pain problem [44]. So overall, biological models that seek an explanation in structural and biomedical abnormalities cannot sufficiently explain chronic pain and the functional disability it causes [45–47]. Recovery of complaints should therefore not only be explained by the nature of the injury and the surgical intervention itself, but also by psychological, social, and contextual factors.

### Fear-avoidance model of chronic pain

Over the years, theories considering psychological factors, such as individual beliefs and behavior, have been proposed. An influential theoretical model in this area is the fear-avoidance (FA) model [48–51]. The FA model proposes that chronic pain may develop when pain-related fear and avoidance behavior persist beyond healing time, or when protective responses generalize to novel stimuli (generalization stimuli) resembling the original fear-eliciting stimulus. More specifically, the model proposes that people who interpret pain as a sign of bodily threat, prioritize control of pain that does not go away, leading to fear and avoidance. When negative affect and harm expectations are present, they might increase the engagement in pain control. In the acute pain stage, these protective behaviors serve to reduce or eliminate a justified threat to the body and are considered adaptive. In individuals with chronic pain, however, a pathoanatomical threat (such as injury or spinal pathology) is usually absent, and the costs of avoidance behavior may start to outweigh its benefits. In addition, fear and avoidance are often not restricted to movements/activities that were initially associated with pain but extend to a range of novel (generalization) stimuli. In essence, this *stimulus generalization* is adaptive because it minimizes the necessity to learn everything anew [52], and contains the ability to detect similarities between related stimuli which may contribute to reducing harm in a dynamic environment [53, 54]. Yet, it also bears an increased risk to respond to false alarm threats (“safe stimuli”), which possibly leads to persistent fear and excessive avoidance behavior [54]. Long-term physical inactivity has, in its turn, a negative impact on the musculoskeletal and cardiovascular systems [55–59]. In addition, avoidance may also lead to the withdrawal of positive reinforcers causing interference with valued life activities, which increases negative affect. In its turn, negative affect may worsen the pain even more. In this way, people can get mired in a vicious circle. However, pain-related fear will not always lead to avoidance behavior. The expression of fear of movement-related pain and avoidance behavior is dependent on context. When the value of another life goal outweighs the value of pain control, avoidance behavior can be inhibited [60]. In that case, valued life goals are prioritized and engagement in daily activities will promote recovery [49, 50, 61, 62]. This might be fostered by positive affect and optimism because they enhance goal-directed efforts and stimulate approach instead of avoidance [63].

### Potential predictors

The factors that predict individual differences in outcomes of surgery in terms of postoperative pain, recovery, and resumption of work are still largely unknown. The existing evidence points towards the role of individual beliefs and behavior, sometimes referred to as the “yellow flags” [64, 65]. More specifically, negative emotions [66], catastrophic (mis)interpretations of pain [67], fear of movement-related pain [68, 69], expectancies towards recovery [70], optimism [63, 71] and intolerance of uncertainty [72, 73] appear to significantly influence functioning after back surgery. Linton and Halldén [74] developed a screening tool, called the Örebro Musculoskeletal Pain Questionnaire (ÖMPQ), for the early identification of individuals who risk developing a persistent pain problem. The ÖMPQ was found to be a clinically reliable and valid instrument [75, 76]. In the same vein, Mannion et al. [77], reported that yellow flags significantly contributed to predicting not only the persistency of the pain but also patient outcomes after surgery in general.

## Methods

### Design

This multisite study has a prospective, longitudinal design in which individuals with radicular pain who undergo a lumbar decompression, will be followed prior to surgery up until 1 year post-surgery. Measurements take place prior to surgery (preoperative measurement), immediately after surgery (postoperative measurement), and 6 weeks, 3 months, 6 months, and 12 months post-surgery (follow-up measurements), see Fig. 1. The expected duration of the entire study is approximately 2 years.

**Fig. 1 Fig1:**
[figure not shown]
Study design. *Note*. The first icon represents the consult with the surgeon, the second one the consult with the research assistant. The third icon (the computer) represents the assessment of the computer task. The fourth icon (the notepad) represents the assessments of the questionnaire. The fifth and last icon, presented in blue, represents the surgery

### Participants

Three hundred individuals with radicular pain will be recruited. Every participant will be planned for back surgery in one of the nine involved Belgian hospitals (i.e., University Hospitals Leuven, Ziekenhuis Oost-Limburg, Noorderhart Mariaziekenhuis, AZ Groeninge, GasthuisZusters Antwerp, Centre Hospitalier de Wallonie picarde, Imeldaziekenhuis, Regional Hospital Heilig Hart Tienen, and AZ Sint-Lucas Ghent). Inclusion criteria are: (a) age between 18 and 55, (b) proper mastery of the Dutch, English, and/or French language, (c) intermittent or constant invalidating lumbosciatica for less than 1 year prior to the planned surgery, operationalized by being on sick leave on the day of the surgery (documented by the surgeon), (d) radicular pain in the leg(s) due to compression, that will be treated surgically by performing a decompression without it leading to fusion and/or fixation, and (e) self-employed or has an employment contract, and is on sick leave for less than 1 year at the day of the surgery. Reasons for exclusion are (based on self-report): (a) being treated (ambulant or residential) for substance abuse, suicidal ideation, or a psychotic disorder in the year before the consult with the surgeon, (b) at least one back surgery in the last 5 years prior to the planned surgery, and (c) presence of a comorbid condition (e.g. a severe neurological deficit, a pulmonary embolism, permanent paralysis, and another pain problem in the limbs), which may affect the pain, the outcome of the surgery, the duration of the rehabilitation, and/or the participant’s capacity to return to work during the course of the study. At the end of the study, participants will receive a gift voucher worth of maximum 40 euros (at a rate of 10 euros per completed follow-up measurement).

### Sample size

Because there are no previous studies available on the prediction of pain severity and work resumption after back surgery that include all variables in our study, an a priori power analysis for multiple linear regression was conducted. This analysis revealed that, in a model with 12 predictors and a numerator degree of freedom of 14, with a power of 90% (an increase of 0.13 in R^2^), a total sample size of n = 167 is needed to detect a medium effect (effect size f^2^ = 0.1494) at an alpha level of 0.05. Considering potential dropouts from follow-up measurements (conservatively estimated at 50%), the aim for inclusion is set at 300 participants. Power calculations were performed in G*Power version 3.0.10.

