## Measurement instruments

### Outcome variables

#### Self-reported work resumption

To measure work resumption, we make a distinction between being fit for work, work resumption, and sustainable work resumption. Being fit for work will be operationalized by not receiving disability benefits. Work resumption will be operationalized by being at work without receiving disability benefits (on a dichotomous scale), and by time to relapse. Time to relapse is defined as the duration of being at work until a participant is on sick leave again. Sustainable work resumption will be operationalized by being at work for at least three consecutive months without receiving disability benefits (on a dichotomous scale). In addition, the duration of work resumption will be measured (on a continuous scale). All these variables will be assessed using custom-made self-report questions. The custom-made questionnaires are presented in Additional file 1. In order to calculate the time to relapse and sustainable work resumption, we will ask the participants to indicate when they were incapacitated from work and when they resumed work. In addition, we will directly ask if the participant resumed work for at least three consecutive months.

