## Statistical analysis plan

Following an intent-to-treat approach, data from all included participants will be analyzed. Descriptive statistics will be used to explore the mean and median scores, and standard deviations of all measures. Depending on the type of dependent variable, we will apply Cox proportional-hazards regression analysis with time-dependent covariates or multiple (logistic) regression analysis, starting with a univariate analysis, followed by a multivariate analysis. If statistical power allows, interaction effect between time and all the predictor variables will also be tested to evaluate if the effect of the predictor variables is consistent in time. Additionally, we will check for site effects with the mixed model regression approach. All variables will be examined for the assumptions required for parametric analyses. Results will be evaluated at *p* < 0.05 significance level. Effect sizes (i.e., odds ratios) and post hoc power will be calculated when appropriate.

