### Primary objectives

Logistic regressions will be performed to examine the effect of preoperative as well as postoperative fear of movement-related pain and avoidance behavior (and their generalization), expectancies towards recovery, expectancies towards work resumption, presence of yellow flags, on return to work at 6 weeks, 3 months, 6 months, and 12 months post-surgery. Next, a time-dependent Cox regression will be performed to examine the effect of the predictor variables on return to work over time. The same analyses will be conducted for the sustainability of work resumption at 3 months, 6 months, and 12 months post-surgery as a dependent variable.

Multiple linear regression analyses will be carried out to examine the effect of the predictor variables on the duration to resume work over time. Log-rank test and Kaplan–Meier plots will be applied to compare rates of work resumption between participants with different profiles (i.e. at work or not during the different measurement moments).

All interaction effects, including the predictor*time interactions, will be explored. Following potential confounders will be included as covariates in each analysis: age, sex, work characteristics, duration of incapacity for work, surgery complication, and the potential influence of the COVID-19 pandemic.

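### The stated 90% power is for a joint linear-regression F-test and does not cover the logistic and Cox tests of sustainable work resumption, among which no deciding analysis is named

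*Protocol article*

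**What the plan says.** The protocol article's Sample size section states that "an a priori power analysis for multiple linear regression was conducted". Its inputs are "in a model with 12 predictors and a numerator degree of freedom of 14", "with a power of 90% (an increase of 0.13 in R^2" and "at an alpha level of 0.05". Its result is that "a total sample size of n = 167 is needed to detect a medium effect (effect size f^2^ = 0.1494". The inclusion target is then set at 300 to allow for 50% dropout.

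The Rationale section makes sustainable work resumption the primary outcome and fear, avoidance and their generalization the predictors of interest. Under Self-reported work resumption, "Sustainable work resumption will be operationalized by being at work for at least three consecutive months", scored as yes or no.

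Under Primary objectives, "Logistic regressions will be performed to examine the effect of preoperative as well as postoperative fear of movement-related pain and avoidance behavior", together with generalization, expectancies and yellow flags, on return to work at four visits. A time-dependent Cox model follows. The same analyses are repeated for sustainable resumption at 3, 6 and 12 months. Linear regression appears under that heading only for the time taken to resume work, and under Secondary objectives for pain, disability and quality of life. The Statistical analysis plan section adds: "Results will be evaluated at *p* < 0.05 significance level".

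**The concern.** Power for a logistic coefficient depends on how many participants fall in the smaller outcome group. For a Cox model it depends on the number of events. The Sample size section uses neither quantity. It uses the variance explained in a linear model by all predictors together. So the 90% belongs to a different outcome scale and to a joint hypothesis. That hypothesis could be rejected through expectancies or yellow flags alone, leaving the fear/avoidance question unanswered.

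The plan also does not say which of the several tests on sustainable resumption decides the primary hypothesis. Under Primary objectives, expectancies and yellow flags stand beside the fear and avoidance terms, although the Rationale section makes them secondary. At stake are a power claim that readers will wrongly attach to the primary question, and an undefined error rate for the main conclusion.

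**Working it through.** **1. Reproducing n = 167.** Effect size: f² = 0.13/(1 − 0.13) = 0.1494, as stated. Noncentral F with λ = f²·N, u numerator df, and N − p − 1 denominator df:

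| Test | N for 90% power |
|---|---|
| u = 14, p = 12 or 14 | 167 (power 0.902) |
| u = 12, p = 12 | 157 |
| u = 1, p = 14, same f² on one coefficient | 73 |

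Only the 14-df joint test gives 167. Even on the linear scale this is not power per coefficient. If the 0.13 is split evenly over 14 terms, each has f² = (0.13/14)/0.87 = 0.0107, and power for one term at N = 167 is about 26%.

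**2. Tests on sustainable resumption alone.**
- Narrow count: 4 constructs (fear, avoidance, and the generalization of each) × 3 visits = 12. Expected false positives under the null: 12 × 0.05 = 0.6. Familywise error if independent: 1 − 0.95^12 = 0.46.
- Wider count: 6 terms (fear pre and post, avoidance pre and post, two generalization scores) × 4 analyses (3 logistic, 1 Cox) = 24. Expected false positives: 24 × 0.05 = 1.2.

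**3. Size of the smaller outcome group.** Analysable: 300 × 0.5 = 150. The Back surgery section cites return rates of 50–90%, and 20% not back at 1 year.
- 90% return: 150 × 0.10 = 15
- 80% return: 150 × 0.20 = 30
- 50% return: 150 × 0.50 = 75
- 80% return and no dropout: 300 × 0.20 = 60

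**4. Model terms (derived, not stated).** Fear, avoidance, two expectancies and yellow flags, pre and post, give 10; two generalization scores make 12. Covariates are age, sex, incapacity duration, complications, at least one work characteristic and three COVID-19 items: at least 8. The total is at least 20 if all enter together. If pre- and postoperative scores go into separate models, the preoperative one has 5 + 2 + 8 = 15. Participants in the smaller group per term: 30/20 = 1.5; with no dropout and 15 terms, 60/15 = 4.

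**5. Detectable odds ratio.** The article gives no target odds ratio, so this is an assumption-based range for one coefficient, per SD of the predictor, unadjusted, two-sided 0.05, 90% power: ln(OR) = (1.960 + 1.2815)/√(n·q·(1 − q)), where q is the proportion not back at work.

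| n | q | ln(OR) | OR |
|---|---|---|---|
| 150 | 0.5 | 3.2415/√37.5 = 0.529 | 1.70 |
| 150 | 0.2 | 3.2415/√24 = 0.662 | 1.94 |
| 150 | 0.1 | 3.2415/√13.5 = 0.882 | 2.42 |
| 300 | 0.2 | 3.2415/√48 = 0.468 | 1.60 |

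Correlation with other terms raises these values. At n = 150 and q = 0.2, power for an odds ratio of 1.5 is about 51%.

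**6. Cox model.** The event is resumption, so the count is larger: 150 × 0.8 = 120 for plain return to work. The detectable hazard ratio for one unadjusted coefficient is exp(3.2415/√120) = 1.34, or 0.74 in the other direction. The article gives no rate for sustainable resumption, so this is not the power of the primary Cox test.

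**The case against.** The strongest reply is that linear regression is run in this study. It is planned for the time to resume work, under the primary heading, and for the three secondary outcomes, where an overall F-test is routine. That stands. A reader might infer that the powered test is never performed, and the article does not support that. What remains is that the power statement does not reach the logistic and Cox tests of sustainable resumption.

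Second, a reader might multiply six terms by all nine logistic and Cox analyses and report 54 tests. Five of those nine concern plain return to work, whereas the stated primary outcome is sustainable resumption. The defensible count is 12 to 24.

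Third, 30 non-returners and 20 terms are tempting as fixed facts. They need the full 50% dropout, 20% non-return, and pre- and postoperative scores in one model. The article calls the dropout estimate conservative and does not say that both sets of scores enter together. The 20% is a 1-year figure for resuming work. Participants must be on sick leave at surgery, and Demographic variables cites 70% non-return among those incapacitated for more than 3 months, so 20% may be too low. Nor can serious overfitting bias be asserted. In simulations with independent terms, 20% non-return and a true odds ratio of 1.5, the average estimate was 1.60 with 15 terms and 1.67 with 20 at n = 150, but 1.56 with 20 terms at n = 300.

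Finally, this is a condensed article on an observational study, and multiplicity handling may sit in a separate plan. That weakens the multiplicity part. It does not rescue the power statement, which is explicit and tied to another test.

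**Conclusion.** The concern holds in this limited form. The 90% applies to a 14-df joint F-test on a continuous outcome and gives no assurance for the primary objective. The article names no analysis that decides that objective, which leaves 12 to 24 tests at 0.05 on sustainable resumption. The test counts rest on how the constructs are scored, and the 46% familywise figure assumes independent tests. The odds ratios of 1.70 to 2.42 rest on 150 analysable, the cited 50–90% return range and an unadjusted single coefficient.

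A reader might infer that the study is underpowered for its primary question. The article does not support that, because it gives no target odds or hazard ratio and the Cox model is better placed than the visit-wise logistic models. The supportable statement is that power for the primary question is unknown. This should be corrected, but it does not invalidate the design.

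**What to change.** Before the data are analysed, name one primary analysis of sustainable work resumption. One suitable choice is the Cox model to 12 months with a single joint test of the fear and avoidance terms, including generalization, at 0.05. Label the visit-wise logistic models, plain return to work, expectancies, yellow flags and interactions as supportive.

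Restate power for that named joint test at 300 enrolled, from expected events over a range of dropout and resumption rates. The single-coefficient figures above show scale only and should not stand in for it. State that the 90% linear-regression figure covers only the continuous outcomes. Penalised logistic fitting and the exact covariate set are optional choices.

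The cost is a change of wording and a short recalculation, with no new data. The downside is that fewer results can be called confirmatory, and the restated power may be less favourable than 90%.

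### The enrolment target of 300 leaves 150 at the stated 50% dropout, short of the 167 stated for 90% power, and the 14 numerator df is not reconciled with 12 predictors

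*Protocol article*

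**What the plan says.** The Sample size section of the protocol article reports that "an a priori power analysis for multiple linear regression was conducted", specified as a test "in a model with 12 predictors and a numerator degree of freedom of 14". The inputs are 90% power, an R² increase of 0.13 (f² = 0.1494) and alpha 0.05. The result is that "a total sample size of n = 167 is needed to detect a medium effect". The next step goes from 167 to the enrolment target: "Considering potential dropouts from follow-up measurements (conservatively estimated at 50%), the aim for inclusion is set at 300 participants". The Participants section repeats the target of 300. Nowhere does the article say that dropouts will be replaced or that fewer than 167 analysable participants would be accepted.

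**The concern.** Two things in this short paragraph do not fit together.

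The first is the step from 167 to 300. A 50% loss halves the enrolled number, and half of 300 is less than 167. The paragraph is the only justification given for the enrolment target, so a target that fails its own dropout assumption means that the stated 90% power is not what the design delivers under that assumption. The Discussion itself names dropout over time as a practical risk, so the assumption matters.

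The second is the pairing of 12 predictors with 14 numerator degrees of freedom. In an F test for an increase in R², the numerator df is the number of coefficients tested, and this cannot exceed the number of coefficients in the model. If each predictor is one coefficient, 12 and 14 do not match. The required number depends on which of them is the tested df.

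**Working it through.** **Inputs, all from the Sample size section:** f² = 0.1494; alpha = 0.05; target power 0.90; 12 predictors; numerator df 14; required N = 167; dropout 50%; enrolment 300.

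**Effect size.** f² = ΔR²/(1 − R²) = 0.13/0.87 = 0.1494. This agrees with the stated value.

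**Reproducing 167.** For the multiple-regression F test, let u be the numerator df, p the number of coefficients in the model, v = N − p − 1 the denominator df, and λ = f² × N. Power is the probability that a noncentral F(u, v, λ) exceeds the 95th percentile of the central F(u, v). The smallest N with power of at least 0.90 is:

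| Numerator df u | Coefficients p | Required N | Power at N = 167 | Power at N = 150 |
|---|---|---|---|---|
| 14 | 14 | 167 | 90.2% | 85.5% |
| 14 | 12 (numbers taken literally) | 167 | 90.2% | 85.5% |
| 14 | 20 | 167 | 90.1% | 85.3% |
| 12 | 12 | 157 | 92.2% | 88.2% |
| 12 | 14 | 158 | 92.2% | 88.1% |

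So 167 reproduces exactly with 14 numerator df. It hardly depends on p: every p from 14 to 22 gives 167. With 12 numerator df the figure is 157 or 158. The calculation was therefore run on 14 df.

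**Checking 300.**

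- Expected completers at 50% dropout: 300 × 0.50 = 150, and 167 − 150 = 17 short.
- Enrolment needed for 167 completers: 167/(1 − 0.50) = 334.
- Enrolment needed if the tested df is 12: 157/0.50 = 314, still above 300.
- The common mistaken inflation, 167 × 1.5 = 250.5 (251), does not give 300 either.
- Largest dropout at which 300 still leaves 167: 1 − 167/300 = 44.3%.

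**Loss of power at 150 completers.** Against the stated 90%: 90 − 85.5 = 4.5 percentage points with 14 df, and 90 − 88.2 = 1.8 points with 12 df.

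**The case against.** A fair defence has four parts.

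- **The shortfall is small and conditional.** It appears only if dropout goes beyond 44.3%, and the section describes its 50% as a conservative estimate. Even at 50%, power stays above 85%. This stands and limits the size of the point. It does not make the stated figures agree: if less dropout is expected, the text should give the rate that 300 covers.
- **The 90% does not describe the main tests.** The power analysis is for linear regression, while return to work and its sustainability are analysed mainly by logistic and Cox regression, and a Cox model can use partial follow-up from people who later leave. This too stands as a limit on the practical consequence. It does not repair the arithmetic that the enrolment target rests on.
- **All included participants will be analysed.** The Statistical analysis plan section says so. But the Sample size section itself inflates for loss to follow-up, so 167 is meant as the number with follow-up data.
- **Twelve predictors can take 14 df.** A reader might infer that 14 numerator df in a 12-predictor model is impossible and that 167 is therefore invalid. The document does not support this. Twelve predictor variables use 14 df if one or two are categorical with three or more levels, and the study collects variables of that kind, such as relationship status, education and type of contract. The article does not list the 12 or their coding, so the explanation can be neither confirmed nor excluded. A condensed article may leave such detail to a fuller document. What remains is that two unequal numbers stand in one sentence without a word to connect them.

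**Conclusion.** The point holds for the enrolment target. On the protocol's own figures, 300 enrolled with 50% dropout gives 150 analysable participants, not the 167 stated as needed. The corresponding power is about 85.5% on the stated 14 df, or 88.2% if the tested df is 12, so 90% is missed under both readings. The loss is modest. This rests on the linear-regression F test, f² and alpha as stated, on dropouts contributing nothing to the analysis, and on no replacement of dropouts.

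The 12 against 14 is a lesser matter: unexplained, and in need of reconciling. It does not show a miscalculation, because 167 is the correct N for 14 df; if the tested df were 12, 167 would be about 10 more than required. Nor can it be concluded that the df is the number to change, since both may be right with only a note on coding missing.

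**What to change.** Rewrite the Sample size paragraph; no additional enrolment is needed.

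1. Replace the claim on power and dropout with one of two statements, both on 14 numerator df: 300 enrolled gives about 85% power at 50% dropout; or 300 enrolled gives 90% power at up to 44% dropout.
2. Reconcile the 12 predictors with the 14 numerator df, for example by saying which predictors take more than one df, if that is the reason. If 12 proves to be the tested df, use N = 157 and 88% power at 150 completers instead.

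The cost is one corrected paragraph and a slightly less favourable statement of power or of tolerated dropout. Design, recruitment and analyses stay as they are.
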